#### Baseline data

The baseline data collected includes patient demographics such as sex, age, work (and work status), arm dominance, height/weight, tobacco and alcohol habits, and list of current diseases, American Society of Anesthesiologists (ASA) grade, mechanism of injury, radiographs, previous surgeries and injuries in the affected shoulder. The following baseline questionnaires will be filled in digitally: Preinjury Disabilities of the Arm, Shoulder and Hand (DASH), University of California, Los Angeles (UCLA) activity scale, European Quality of Life, 5 Dimensions, 5 Levels (EQ-5D-5L) scores. Shoulder pain via an 11-point visual analog scale (VAS).

#### Primary outcome measure

The DASH score at 1 year.

For the upper extremity, the DASH score is the most used general PROM and it is validated and reliable for use in a multitude of pathologies in the upper extremity [36–38]. It has been validated for use in several upper extremity disorders [39] and has been cross-culturally adapted into Swedish, Danish, Norwegian, and Finnish populations [40].

#### Secondary outcome measures

Upper extremity function and symptoms will be measured by the DASH at all timepoints.NCS at all timepoints.General health status questionnaire measured by the EQ-5D-5L.Shoulder pain will be assessed by an 11-point VAS, where patients are asked to assess their overall pain in the arm from 0 to 10 in a day.Healing will be assessed via routine radiographs by the participating centers at 1 year. Radiographic union is defined as cortical bridging between the medial and lateral fragments. Symptomatic nonunion is defined as a lack of radiographic union in combination with clinical signs of nonunion (movement at the fracture site, persisting pain) [41]. Radiographic nonunion without symptoms will be recorded but not considered an adverse event.Malunion of some degree is expected with nonsurgically treated clavicles and is therefore characterized by being symptomatic or not [42].Return to work collected from participants at all timepoints.Anchor questions in the form of the PGIC at all timepoints presented with 7 response options and analyzed as a 7-point Likert scale.Adverse events (AEs) after treatment will be recorded and include (see Table 2).

**Table 2 Tab2:** Safety outcomes

Adverse event		
Surgical		Non-surgical
Deep infection (FRI)	Vascular injury or injury to brachial plexus	Symptomatic nonunion**
Superficial infection	Fixation failure	ACJ arthritis
Hardware irritation	Nonunion	Impingement
Supraclavicular nerve injury*	Scar or wound issues	
Serious adverse events (SAEs)—defined by the US Food and Drug Administration (FDA) [43] as any untoward medical occurrence that results in death, is life-threatening, results in hospitalization, significant disability, or permanent damage, or requires intervention to prevent impairment or damage. Major adverse cardiovascular events (MACEs) is a type of SAE that is defined as acute myocardial failure (AMI), stroke, cardiovascular death, heart failure (HF), and unstable angina		

^*^Prevalence varies greatly between studies [44, 45]

^**^Asymptomatic nonunion is not counted as an adverse event for the purpose of this study but will be recorded

For the purpose of this study, we will grade the severity of complications into five levels, according to the modified Clavien–Dindo classification [46], which was originally aimed at gastroabdominal surgical complications, but it has been adapted for use in orthopedic complications with a simplified severity grading I–V, where V is death [47]. They do not include complications pertaining to anesthesia.

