## Background and rationale

Clavicle fractures constitute 3–4% of all fractures in adults [1, 2]. Midshaft fractures are most common (65–82%) followed by lateral (12–30%) and finally medial (2–6%) fractures. Most lateral clavicle fractures (LCFs) are extraarticular. There is a typical bimodal pattern consisting of young males and elderly women. The injury pattern is often sports-related (dominated by cycling) or traffic accidents in the young or simple falls in the elderly [3–6]. LCFs are often classified according to Neer, modified by Craig, where types II and V are unstable and equivalent to a coracoclavicular (CC) disruption (see Supplementary material 1, S1) [7, 8].

High-quality trials comparing treatment of displaced extraarticular lateral clavicle fractures (LCFs) are scarce. No published RCT has included enough patients to provide sufficient statistical power to detect clinically meaningful differences.

The desire to restore the anatomy and to avoid nonunion have been the main reasons for surgical treatment of displaced LCFs. Nonunion rate after nonsurgical treatment has been reported as high as 33% [7–10]. Surgical treatment of an LCF commonly consists of plate fixation (anatomical locking plate or hook plate) with or without CC fixation [11–17]. Complications after surgical treatment are relatively common, particularly when using hook plates, which can cause subacromial erosion, osteolysis, and rotator cuff injury [18–21]. Hook plate removal is advocated after about 3 months, and many regard this secondary procedure as part of the treatment algorithm [22–24].

However, several systematic reviews and meta-analyses have reported no difference in patient-reported outcome measures (PROMs) between surgical and nonsurgical treatment, even in cases with radiological nonunion [10, 25, 26]. Two RCTs have attempted to provide evidence in this regard, but both were underpowered [27].

The aim of this study is to determine if nonsurgical treatment is noninferior to surgical treatment of Neer type II and V displaced LCFs.

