### Interim analysis

A blinded sample size re-estimation [63] will be performed in the case of slow recruitment to determine if the target sample size can be adjusted. The inclusion rate will be monitored by the Data and Safety Monitoring Committee (DSMC) (composition is outlined below) as well as the TSC.

There will not be an interim analysis on the primary outcome (DASH), and the reasoning is that no study has as of yet indicated a clinically significant difference in outcome between surgical and nonsurgical treatment. However, the DSMC will monitor the complication frequency in both treatment arms at predefined intervals and may advise the TSC on premature termination of the study if there is a gross imbalance in complication frequency. The DSMC will schedule a meeting shortly after study enrollment begins to agree on monitoring frequency. The DSMC will operate independently from the rest of the study group.

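### Table 2 defines nonunion differently for surgical and nonsurgical care and lists ACJ arthritis and impingement on one side only, so the complication comparison between arms can partly reflect unequal definitions

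*Protocol article*

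**What the plan says.** Under Secondary outcome measures, the Protocol article refers the reader to Table 2 for adverse events: "Adverse events (AEs) after treatment will be recorded and include (see Table 2"). The table has one column headed Surgical and one headed Non-surgical.

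- The Surgical column has eight entries. One is nonunion, with no qualifier and no footnote mark.
- The Non-surgical column has three: "Symptomatic nonunion" (with a footnote mark), "ACJ arthritis" and impingement.

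The footnote reads: "Asymptomatic nonunion is not counted as an adverse event for the purpose of this study but will be recorded". The text above the table gives the same rule, "Radiographic nonunion without symptoms will be recorded but not considered an adverse event", and a definition: "Symptomatic nonunion is defined as a lack of radiographic union in combination with clinical signs of nonunion".

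Three other sections bear on this. Background and rationale describes complications of surgery as fairly common, "particularly when using hook plates, which can cause subacromial erosion, osteolysis, and rotator cuff injury", and the Surgical treatment section permits hook plates. Under Interim analysis, the DSMC follows complications in both arms and "may advise the TSC on premature termination of the study if there is a gross imbalance in complication frequency". Under Statistical analysis, complications are to be presented descriptively.

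**The concern.** A comparison of event frequencies between arms is interpretable only if an event that can occur in either arm is defined and looked for in the same way in both. Table 2 departs from this for nonunion and for ACJ arthritis and impingement.

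A site that follows the table counts a symptom-free nonunion after surgery as an adverse event. A site that follows the text does not. A site that uses the columns as its checklist is prompted for impingement after nonsurgical care but not after a hook plate.

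Two uses of the data are at stake: the descriptive complication results, and the DSMC's review. An imbalance in complications is the only ground for early termination that the Interim analysis section names.

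**Working it through.** **Step 1. Compare the entries for events possible in both arms.**

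| Event | Surgical column | Non-surgical column | Elsewhere in the article |
|---|---|---|---|
| Nonunion | Listed, unqualified, no footnote mark | Symptomatic only, footnote mark | Text and footnote: asymptomatic nonunion is not an adverse event, with no restriction to one arm |
| ACJ arthritis | Not listed | Listed | – |
| Impingement | Not listed | Listed | Background: hook plates can harm the subacromial space and rotator cuff |

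The first row is a contradiction, because the table and the text cannot both be followed for a symptom-free nonunion after surgery. The other two rows are one-sided prompts. Settling the nonunion wording in favour of the text leaves them in place.

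**Step 2. Direction.** An unqualified surgical nonunion entry raises the surgical count. Listing ACJ arthritis and impingement only under Non-surgical raises the nonsurgical count. The two work against each other.

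**Step 3. How large could each be?** The protocol gives no figure for the safety comparison, so there is none to reproduce. Its only usable input is 100 patients at 1:1, or about 50 per arm. Everything else here is an assumption, chosen to show a range:

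- The true event rate is the same in both arms.
- Sites follow the columns literally.
- All 50 patients per arm are assessed.

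Expected counted events = 50 × true rate × share counted under that column.

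As a yardstick, the last column of the table gives the chance that a two-sided Fisher test reaches p ≤ 0.05. It sums Bin(i; 50, p₁) × Bin(j; 50, p₂) over all pairs (i, j) with Fisher p ≤ 0.05, where p₁ and p₂ are the counted rates. The protocol sets no such threshold.

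| Assumed true rate, both arms | Assumed symptomatic share | Counted, surgical v nonsurgical | Chance of p ≤ 0.05 |
|---|---|---|---|
| Nonunion 10% | 25% | 5 v 1.25 | 15.9% |
| | 50% | 5 v 2.5 | 6.3% |
| | 75% | 5 v 3.75 | 2.6% |
| | same definition in both arms | 5 v 5 | 1.8% |
| Nonunion 20% | 25% | 10 v 2.5 | 50.8% |
| | 50% | 10 v 5 | 19.5% |
| | 75% | 10 v 7.5 | 6.0% |
| | same definition in both arms | 10 v 10 | 2.8% |
| ACJ arthritis or impingement 5% | – | 0 v 2.5 | 3.8% |
| 10% | – | 0 v 5 | 38.4% |
| 20% | – | 0 v 10 | 95.2% |

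Example: at 20% nonunion with half symptomatic, 50 × 0.20 × 1 = 10 are counted after surgery and 50 × 0.20 × 0.5 = 5 after nonsurgical care.

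**Step 4. Net effect over these ranges.** The nonunion wording adds between 5 − 3.75 = 1.25 and 10 − 2.5 = 7.5 events to the surgical side. The one-sided prompts add between 2.5 and 10 to the nonsurgical side. The net artefact therefore runs from 7.5 − 2.5 = 5 extra surgical events to 10 − 1.25 = 8.75 extra nonsurgical events. At 20% nonunion, half symptomatic, and 10% ACJ arthritis or impingement, it is 5 − 5 = 0. Neither sign nor size can be fixed from the documents.

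**The case against.** The other side has a good deal to say.

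- The text and the footnote state one nonunion rule without reference to arm. The unqualified surgical entry may simply be a loose label.
- The word that introduces Table 2 suggests examples, not a closed list. Nothing forbids recording impingement after surgery.
- The definition of serious adverse events and the severity grading are common to both arms.
- Complications are descriptive. The DSMC is independent and may only advise, and its working rules may sit in a charter that is not shown.

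All of this softens the point. None of it supplies a common definition: the label still contradicts the text, and the one-sided prompts remain.

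A reader might also infer more than the documents support:

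- *That the comparison is unequal by construction.* This would require the columns to be closed lists and the DSMC to be tied to Table 2 counts. The article states neither.
- *That eight entries against three shows bias.* Most of the surgical entries, such as infection, hardware and wound problems, can arise only from an operation, so listing them there is reasonable. The defect is confined to events possible in both arms.
- *That about 16 patients have an undefined event status, from 33% of 50 = 16.5.* The 33% is an upper figure for nonunion after nonsurgical treatment, where the table entry is clear. The ambiguous entry is the surgical one, and no surgical nonunion rate is given.
- *That a patient who crosses over for non-healing yields no listed event.* Severe persisting pain without healing may meet the symptomatic nonunion definition, and the operation may meet the serious adverse event definition. The article does not say how such cases are classified, but it does not exclude them.

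**Conclusion.** The point holds in limited form. Table 2 contradicts the text on nonunion, and it lists two events on one side only although the article's own background gives reason to look for related harm after surgery. As written, the arm comparison of complications, including the one the DSMC may act on, can partly reflect unequal definitions.

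The illustration shows that either discrepancy alone could matter with 50 per arm, but also that the two could cancel. It rests on assumed equal rates, assumed symptomatic shares and literal use of the columns. It is neither an estimate of bias nor evidence that the trial would be stopped wrongly. The primary DASH analysis and the sample size are not touched.

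**What to change.** 1. Change the surgical nonunion entry to symptomatic nonunion with the same footnote, so that table and text agree. Keep recording asymptomatic nonunion in both arms as a non-event.
2. Record ACJ arthritis, impingement, and subacromial or rotator cuff lesions in both arms.
3. Tabulate all adverse events by randomised arm, including those after crossover surgery, and show crossover surgery for non-healing on its own line.
4. State that the DSMC's imbalance review uses this common list.

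Surgery-specific entries (infection, hardware, wound) can stay as they are, provided they are also recorded after crossover surgery.

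The cost is a revised Table 2 and adverse-event form, a sentence in the DSMC's working rules, and a check of events already recorded. Recruitment began on 1 September 2025, but the article gives no enrolment count, so the extent of that check is not known. No added visit or trial procedure is intended.

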#### Surgical treatment

The method of fixation can include plates (anatomic locking plate or hook plate) and screws ± CC fixation or CC fixation alone [33]. The plate will be applied via a supraclavicular approach to the lateral clavicle with screws in the proximal and distal fragments following basic principles of fracture fixation. The exact technique, type of plate, and CC fixation will be the treating surgeon’s choice and will be recorded.

Postoperatively, the arm will be placed in a sling, and unloaded exercises will commence from day one. The sling is initially used for comfort and can often be discarded approximately 1 to 2 weeks postoperatively. The type of sling and continued postoperative exercise regimen and physiotherapy will continue according to the recommended rehabilitation protocol, as described in the nonsurgical treatment above.

The level of experience of the operating surgeon will not be defined, but they must be familiar and experienced with the fixation method and material they are using. Each participating center will take responsibility to ensure that this is followed.

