## Discussion

The ScanDiLaC study will compare the effectiveness of surgical versus nonsurgical treatment of displaced Neer type II and V lateral clavicle fractures and attempt to define the appropriate timing of early crossover surgery. The optimal treatment for the unstable Neer types II and V is not clear from the literature.

The TSC made a mutual, pragmatic decision to not include patients above 65 years old in the study, as no one would consider performing primary surgical treatment for this age group.

To achieve sufficient power in this study, we would need to ensure an adequate inclusion rate. In 2024, 320 displaced LCFs were registered in the Swedish Fracture Register [64] across all of Sweden. If only the currently recruiting sites are included and consider the possibility of incorrectly registered fractures [65], as well as the expected success rate of inclusion for each patient, we have estimated an optimistic possible inclusion rate of 31–32 patients per year in Sweden. We expect that the number will be matched when Denmark, Norway, and Finland are combined. This emphasizes the need for this multicenter collaboration between Nordic countries, where there are comparable healthcare systems and cultural and demographic similarities. Despite this, there are local differences in treatment, particularly with surgical treatment, where the use of hook plates has been a topic of much debate among orthopedic surgeons [18–21]. Many sites use hook plates, whereas others do not. This leads us to take a more pragmatic approach and allow both hook plates and anatomical locking plates with or without CC fixation. Since most surgeons consider removal of the hook plate after bony healing to be a mandatory part of the treatment algorithm [19], this will not be considered a complication in the context of this study.

Given the possibility of surgical treatment differing between sites, there is a risk of bias in the surgical group where it would be possible that a single site only randomizes to surgical treatment. To minimize this risk, the randomization will be stratified by sites in smaller permuted blocks of 2 and 4 to limit the risk of open blocks in multiple sites, as the expected number of patients included per site is low. This reduces the risk of allocation bias.

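### Anaesthesia complications are left out of the severity grading, hook-plate removal is not a complication, and no listed outcome counts further operations, so operative burden is undercounted, mainly in the surgical arm

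*Protocol article*

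**What the plan says.** All references are to the Protocol article.

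- **Severity grading (Secondary outcome measures, after Table 2).** Complications are graded I to V on a modified Clavien–Dindo scale, with the restriction "They do not include complications pertaining to anesthesia".
- **Hook-plate removal (Discussion).** Because most surgeons see removal as a required step of the treatment, "this will not be considered a complication in the context of this study". The Background describes the same procedure in these terms: "Hook plate removal is advocated after about 3 months, and many regard this secondary procedure as part of the treatment algorithm".
- **Hook-plate use.** The Discussion says "Many sites use hook plates, whereas others do not". Under Surgical treatment, "The exact technique, type of plate, and CC fixation will be the treating surgeon’s choice and will be recorded". No expected share of hook plates is given.
- **Adverse events (Secondary outcome measures, Table 2).** The list opens with "Adverse events (AEs) after treatment will be recorded and include (see Table 2"). It names infection, fixation failure, hardware irritation, nonunion and other items. It has no entry for reoperation, implant removal or crossover surgery. An SAE is an untoward occurrence that, among other criteria, "results in hospitalization, significant disability, or permanent damage, or requires intervention to prevent impairment or damage". MACE is named as a type of SAE.
- **Crossover.** Patients in the nonsurgical arm may move to surgery at the 6-week visit, with the operation within 3 weeks of the decision.
- **Use of the counts.** Statistical analysis presents complications descriptively. Interim analysis lets the DSMC advise early termination if complication frequency differs grossly between the arms.

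**The concern.** The trial asks whether nonsurgical treatment is noninferior to surgery on DASH at 1 year. If it is, much of the argument for it will rest on the operations and harms that patients avoid. That makes the safety tables more than a formality, and since they are descriptive, the counting rules largely determine what they show.

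Two of these rules take out items that arise only from operating: complications of the anaesthetic (from the graded complications) and removal of a hook plate (from complications altogether). A removal is itself an operation. No other listed outcome picks it up, and the same holds for unplanned reoperation and crossover surgery. A reader of the final report could not tell from the listed outcomes how many operations each allocated arm underwent. It is also unclear whether the anaesthesia restriction carries over to the complication frequencies that the DSMC sees.

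**Working it through.** **1. Denominator.** Inputs from Sample size: margin 10.4, SD 14.3, one-sided alpha 0.025, power 90%, attrition 20%.

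- Per arm: n = 2 × (1.960 + 1.282)² × 14.3² / 10.4² = 2 × 10.51 × 204.49 / 108.16 ≈ 39.7, so 40 per arm and 80 in total, as the plan states. An exact noncentral-t check gives 89.5% power at 40 per arm, close enough to the target.
- With attrition: 80 / (1 − 0.20) = 100, as stated. At 1:1 this is 50 per arm randomized and 40 per arm evaluable.

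Nothing below changes these figures.

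**2. Does any listed outcome count a further operation?** The Abstract, Primary outcome measure, Secondary outcome measures with Table 2, and Exploratory outcomes were read for such an item. They list DASH, NCS, EQ-5D-5L, pain VAS, UCLA activity, PGIC, healing, malunion, return to work, AEs/SAEs and cost-utility. None is a count of operations.

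**3. Would the AE or SAE route catch each event?**

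| Event | Graded complication | Table 2 AE/SAE | Listed operation count |
|---|---|---|---|
| Serious anaesthesia event, including MACE | No (excluded) | Yes, as SAE | – |
| Non-serious anaesthesia event | No (excluded) | Not named; possible, since the list is open-ended | – |
| Planned hook-plate removal | No (ruled not a complication) | No; an intended step is not untoward | None |
| Unplanned reoperation | Through its cause (e.g. fixation failure, infection) | Through its cause, or as SAE | None |
| Crossover surgery (nonsurgical arm) | Not as such | Not as such; symptomatic nonunion is an AE | None |

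The clear gaps are planned removal, which no listed outcome captures, and the grade of anaesthesia events.

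**4. Timing.** The Background puts removal at about 3 months. Crossover surgery falls at about 6 + 3 = 9 weeks at the latest. Both lie inside the 1-year horizon of the primary outcome.

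**5. Size.** The hook-plate share h is not given. Assume that every hook plate is removed, so that uncounted second operations = h × N:

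| h | N = 50 randomized | N = 40 evaluable |
|---|---|---|
| 10% | 5 | 4 |
| 25% | 12.5 | 10 |
| 50% | 25 | 20 |
| 75% | 37.5 | 30 |
| 100% | 50 | 40 |

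Per patient allocated to surgery this is 5/50 = 0.1 to 50/50 = 1.0 further operations. No anaesthesia complication rate is given, so that part has no figure.

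**The case against.** **Grading is not recording.** The anaesthesia sentence sits in the grading paragraph and may only describe the adapted scale. The AE list is open-ended, the Abstract promises that all complications will be reported, and the SAE definition has no anaesthesia exclusion. This stands. A reader might infer that the harms of surgery as a whole are understated, or that the sentence contradicts Table 2. The document supports neither: serious anaesthesia events still qualify as SAEs, and an SAE without a severity grade is not a contradiction. Nor is there any basis for supposing that a listed nerve injury would drop out of the grading because of its cause, since the document has no such attribution rule.

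**Further operations can be reconstructed.** Plate type is recorded. The timing of crossover must be known, because crossover outside the window is a protocol violation. Most causes of unplanned reoperation are listed events. This stands in part: the raw material may exist, but plate type shows exposure, not whether and when removal took place.

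**A condensed article may leave tabulation to the full protocol or the SAP.** For a table of secondary procedures alone, this would suffice. It does not cover the two exclusions, which the article itself states as rules. The missing operation count matters because of the removal rule.

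**The direction is not one-sided.** This also stands. Crossover operations and their anaesthetics in the nonsurgical arm go uncounted too. Table 2 lists nonunion for surgery but only symptomatic nonunion for nonsurgical treatment, which could work against surgery. A reader might conclude that the whole safety comparison is tilted towards surgery, but the net direction is not established.

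**The DSMC is not restricted to graded events.** Correct: Interim analysis does not say so. It also does not say that anaesthesia events are included, which is why a clarifying statement is needed.

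**Conclusion.** The concern holds in a limited form. Two written rules, together with the absence of any listed outcome for further operations, mean that graded complications and operative burden are undercounted. The rules on anaesthesia and hook-plate removal act mainly on the surgical arm; crossover operations are uncounted in the nonsurgical arm. For anaesthesia, the loss is the severity grade and possibly the non-serious events. For planned removal, the loss is the event itself.

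The range of about 5 to 50 second operations among 50 surgical patients rests on two assumptions: a hook-plate share of 10% to 100%, and removal of every hook plate. It is an illustration, not an estimate. Treating planned removal as an expected step is defensible, and the article discloses the rule and its reason. The primary DASH analysis and the sample size of 80 evaluable and 100 randomized are not affected. The change should be made because it is cheap and bears directly on how a noninferior result would be read, but the trial's main conclusion does not depend on it.

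**What to change.** 1. Replace the anaesthesia restriction in the severity-grading paragraph. Anaesthesia complications of any index, crossover or removal procedure are graded with the rest or, if the adapted scale cannot take them, reported as a separate count, in either case by allocated arm.
2. State that AE and SAE recording, and the complication frequencies given to the DSMC under Interim analysis, include these events.
3. Keep planned hook-plate removal outside the definition of a complication. Add a secondary descriptive outcome: any further operation on the clavicle or shoulder within 1 year, by allocated arm, split into planned removal, unplanned reoperation and crossover surgery.

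None of this alters treatment, the primary analysis or the sample size. The cost is protocol wording, one added REDCap item per further operation, and slightly higher reported counts, mainly in the surgical arm. Recruitment began on 1 September 2025 and is expected to run to 31 December 2028, so most of the data can still be collected prospectively; patients already enrolled would need the item completed at a later visit or from records.
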